### BA Condition

#### Behavioral Weight Loss

Behavioral weight loss groups will be based on the Diabetes Prevention Program (DPP) [24]. A team dietitian will lead 8 of the 16 Intensive Treatment sessions and 3 of the 6 Maintenance sessions. During the Intensive Treatment phase, participants will receive extensive instruction and practice in self-monitoring of caloric and fat intake. Participants will receive calorie goals that are estimated to produce a weight loss of 1–2 pounds per week [i.e., (starting weight × 12) – 500 kcal]. All participants will be given a goal for daily total fat intake in grams that is based on 25% of total calories from total fat. Participants will self-monitor fat and calories daily for 18 weeks and then one week every month for the following 6-months. Participants will be encouraged to work slowly toward regular self-monitoring, beginning with 2–3 days and working up to 5–7 days over the first 16 weeks. Participants who have difficulty tracking their dietary intake and physical activity will be given modest goals with suggestions to increase tracking gradually. Participants will receive assistance to individualize the study diet based on their usual dietary habits. Participants will be given diet diaries for self-monitoring, the "DPP Fat Counter," a guide of nutrition information for hundreds of foods, and multiple resources for obtaining additional information on areas of concern, including eating out and other social activities and recipes. Self-monitoring diaries will be reviewed by the registered dietitian and returned with suggestions for change and positive feedback. Although the original DPP protocol is based on a low-fat diet, this has been updated to include suggestions to decrease detrimental fats preferentially, namely saturated and *trans*-fats, and to substitute whole grains in place of refined carbohydrate foods to match current dietary recommendations put forth by the United States Department of Agriculture Dietary Guidelines for Americans and the American Heart Association Dietary Guidelines [25-27].

The exercise physiologist will lead 8 of the 16 Intensive Treatment group sessions and 3 of the 6 Maintenance sessions. Participants will work toward the goal of 60 minutes of moderate physical activity on 5 days/week. While walking will be encouraged and pedometers provided, participants will also be encouraged to increase their engagement in any of their preferred physical activities. Participants will be lead through a brief moderate physical activity in each session following didactic content. Examples include group walks, pilates, aerobics, and yoga. See Table 5 for the complete list of group topics.

**Table 5 T5:** Content of group sessions during Intensive Treatment (16 sessions) and Maintenance (6 monthly sessions) phases.

**Session #**	**Group Content**
1 D&E	Session 1: Welcome to the Lifestyle Balance Program
2 D	Session 2: Be a Fat Detective
3 E	Session 3: Being Active: A Way of Life (group walk)
4 D	Session 4: Three Ways to Eat Less Fat
5 E	Session 5: Move Those Muscles
6 D	Session 6: Healthy Eating
7 E	Session 7: Creating a Cardiovascular Program; Building Motivation
8 D	Session 8: Taking Charge of What's Around You
9 E	Session 9: Talking Back to Negative Thoughts
10 D	Session 10: Tip the Calorie Balance (group walk)
11 E	Session 11: The Slippery Slope of Lifestyle Change
12 D	Session 12: Problem Solving Diet and Physical Activity
13 E	Session 13: Jump Start Your Activity Plan (group walk)
14 D	Session 14: Four Keys to Healthy Eating Out
15 E	Session 15: You Can Manage Stress
16 E	Session 16: Ways to Stay Motivated
M1 D	Month 1: Food Cues
M2 E	Month 2: Staying Active on Vacation and Holidays (group walk)
M3 D	Month 3: Vitamins and Supplements
M4 E	Month 4: Muscle Training (group practice)
M5 D	Month 5: Food tasting
M6 E	Month 6: Maintaining Motivation After the Program

Note. D = dietitian-led group E = exercise physiologist-led group

#### Behavioral Activation

The treatment protocol for individual sessions is based on brief behavioral activation treatment as developed by Lejuez and colleagues [14]. Each session will emphasize behavioral activation strategies for depression and how the behavioral activation approach can lead to a more enriching active lifestyle (See Table 6 for individual session content) [14,28,29]. A Master's or doctoral level counselor will conduct all 10 of the individual counseling sessions and all 10 of the 20-min telephone sessions. A total of 20 sessions (in person and telephone) are devoted to behavioral activation strategies because efficacy with this protocol has been established in 20–24 sessions [28].

**Table 6 T6:** Content of behavioral activation individual sessions during Intensive Treatment phase.

**Session #**	**Behavioral Activation Content**
1	Getting Started: How depression affects you
2	Create an environment that supports you; behavioral contracting support
3	Activity hierarchies
4	Reviewing Activity Experiments
5	Avoidance As A Habit
6	The Power of ACTION
7	Rumination and Mindfulness
8	Mood Dependence
9	Progress check: Recycle experiments for difficult behaviors
10	Continued Progress: Behavioral Activation on your own

Participants will first be educated about how depression affects them from a behavioral activation perspective. Then, the following behavioral activation skills will be taught: 1) self-monitoring of daily activities and moods; 2) identification of relationships between daily activities and mood; 3) behavioral contracting; 4) identification of values and goals within a variety of life areas including relationships, employment/career, hobbies/recreation, physical/health issues, and spirituality; 5) developing an activity hierarchy in which 15 activities consistent with life goals are rated ranging from "easiest" to "most difficult" to accomplish; 6) regular completion of a master activity log and behavioral checkout to monitor progress as the participant moves through the hierarchy in a progressive manner, moving from the easier behaviors to the more difficult; 7) recognition of avoidance patterns and how they affect mood; and 8) continued assessment of progress and modification of goals as necessary. Earlier sessions will be used to introduce these components and later sessions will include both strategies for increasing success in achieving reasonable life activity goals and for modifying unrealistic or overly difficult activity goals. Behavioral activation for depression is not meant to specifically target weight loss as a goal. Instead, it will address the processes underlying weight dysregulation, including mood regulatory eating, avoidance, and inactivity. Addressing these factors in advance of dietary and physical activity prescriptions may be essential to progress toward weight loss goals during the weight treatment program that follows.

During the Maintenance phase, counselors will contact participants monthly for 20-min phone calls for 6-months and quarterly for one year. As Lejuez and colleagues [14] describe, once participants have progressed to become more skilled at behavioral activation, sessions may become shorter and/or administered by phone. Phone contacts will be used to provide support for continued progress, reinitiate self-monitoring, recycle through the activation process when needed, and keep contact information up-to-date.

### ST Condition

#### Behavioral Weight Loss

Although the timing of the group visits will differ between conditions, the content of the group weight loss intervention in the ST condition will be identical to the BA condition as described above.

#### Attention Control (Health Education)

A health educator with no training in behavior therapy or psychological counseling will conduct all 10 individual sessions during the Intensive Treatment phase and all 20-minute phone calls during the Maintenance phase. Health education sessions were added to the ST condition to serve as an attention control for the nonspecific effects of behavior therapy. An attention control is designed to simulate a behavioral intervention, providing the same amount of contact as the individual counseling in the BA condition, but is not believed to be an effective treatment for depression [30]. This attention control condition lacks components of behavioral activation that are considered integral to its success. The content of the attention control sessions is designed based on prior research demonstrating that provision of information is not sufficient to change behavior [31-37]. Health information about topics relevant to women's health will be discussed. Participants will select from 19 different health education and well-being topics including body composition analyses, menopause, skin health, finances, dressing for different body shapes, and proper footwear (see Table 7 for the full list of topics). To enhance attendance, participants will be informed that the visit will be for a "weigh in" and health education counseling. The health educator will develop a supportive relationship with the participant, provide health education, but will avoid problem solving or counseling with the participant for depression treatment. When participants have specific questions regarding goals or seek advice, they will be referred to their group leader.

**Table 7 T7:** List of topics for standard treatment individual sessions during Intensive Treatment phase.

**Session #**	**Standard Treatment Content**
1	Body Composition Analyses
2	Vitamins for Women: Making sense out of vitamins
3	Menopause: Your survival guide
4	Breast self-exams: Learn how (and why) to perform a breast self-exam regularly
5	Sexual health
6	Skin health: Have your UV photo taken
7	Bone health
8	Footwear for physical activity: Those aching feet
9	Back pain: Oh, my aching back
10	Heartburn and GERD (gastroesophageal reflux disease)
11	Arthritis
12	Alcohol safety: should I be drinking to my health
13	Dementia: Forget where you put your keys again
14	Heart attack: How do I know if I'm having one
15	Home safety
16	Going green
17	What every woman should know about finances
18	Dress for your body type

During the Maintenance phase, health educators will contact participants monthly for 20-minute phone calls for 6 months and quarterly for one year. Calls will be for the purpose of fostering motivation to attend the 1- and 2-year follow-ups as well as to provide educational material on women's health issues.

### Participant Safety

All eligible participants must receive permission from their primary care physician to participate in the study. Depression safety precautions include having participants complete a BDI-II at every individual and group visit, (except when there is an individual and group visit in the same week) to assess depression levels and suicidality. If a participant reports active suicidal ideation with intent, she will be referred for psychiatric treatment and/or escorted to the Emergency Department at UMM. The PI, a licensed clinical psychologist, will review depression severity scores (BDI-II) of all participants on a weekly basis. If a participant's depression symptoms elevate to 30 or higher on the BDI-II (i.e., severe depression) during treatment, alternative treatment will be deemed clinically necessary and that participant will be referred to the appropriate service. Participants who remain depressed (BDI-II > 12) at the end of treatment will receive written materials about depression treatment options and a list of referrals for depression treatment services.

To minimize risks associated with increasing physical activity, intervention personnel will screen participants at each encounter point to assess symptoms that would increase the risk of physical activity and to report concerns as appropriate. In the case of a concern, the study physician and the participant's primary care physician will be consulted. The nutritional adequacy of the diet will be monitored by our senior nutritionist. If there is concern about a participant's nutrient intake, a report is sent to the participant's primary care physician with the area of concern highlighted and appropriate advice provided by our clinical nutritionist.

Safety monitoring procedures are documented in a standard protocol and overseen by the PI and project director. Any adverse events are reviewed by the study physician within 24 hours. If he deems that the adverse event warrants escalation, the data safety monitoring board (DSMB) will then be notified. Unanticipated adverse events or anticipated adverse events that require medical treatment will be reported to the internal review board. All adverse reactions reported by participants will be documented by intervention providers and reviewed on a monthly basis by the PI and project director. Participants will be referred to their healthcare provider for a medical evaluation and follow-up as needed or recommended by the DSMB. The internal review board, the funding agency and the DSMB will be notified of serious adverse events within 48 hours.

### Retention

A participant tracking system will be used to assure that participants are contacted on a timely basis to obtain study data. Participants are also provided a $50 incentive at baseline, 6-months and 1- and 2-year follow-ups for completion of data collection visits. If they are unable to attend, a home visit will be arranged. Following a missed intervention class, participants will receive class materials by mail. Regular telephone contact with individual BA therapists and ST health educators (monthly during the last 6 months of year 1 and every three months during year 2) will help to keep participants engaged in the program and provide an opportunity to obtain updated contact information. If an individual therapist or health educator is concerned about a participant withdrawing, he or she will speak individually with the participant and attempt to address reasons for disengagement or drop-out. For the purposes of retention, at least three alternative contacts, individuals (e.g., family members, friends) who could provide the participant's contact information if it changes, are collected.

### Sample Size Considerations and Statistical Analyses

#### Sample Size

This study will randomize 174 participants into two conditions (87 per condition) who will be followed for 2 years. We expect approximately 90% power for detecting differences in weight between the conditions assuming a weight change difference of 3.1 kg at 1-year (standard deviation = 5.5 kg) and a 25% loss-to-follow-up rate. This projected data for group differences was taken from pilot data at 6 months and projected to one year based on the original DPP weight change data. The standard deviation was a conservative value chosen from a range of successful lifestyle intervention studies [38-40].

### Primary and Secondary Hypotheses-Analysis Plan

The primary outcome compares body weight between the two randomized groups at 6-months and 1-year follow-up using an intent-to-treat analysis. Linear mixed modeling, using SAS PROC MIXED [41] will test time and group interactions to asses whether within-subject change in body weight differs by condition. Analyses will also be conducted to examine whether there is a dose-response relationship between attendance and outcome, where dose is defined in terms of number of sessions attended. In addition, we will model percent change in body weight at 6-, and 12-months using a similar model.

Secondary outcomes will compare the conditions on depression scores, physical activity, daily caloric intake, treatment adherence (session completion), quality of life score, waist circumference, blood pressure, C-reactive protein and serum lipids at 6-months and 1- and 2-years. Analyses for these outcomes will be similar to those conducted for body weight. To explore proposed mechanisms of change, longitudinal associations of body weight and depressive scores, treatment adherence, and physical activity will be modeled using structural equation modeling [42]. Reciprocal influences of body weight and other factors over time will be modeled in structural equation modeling using nonrecursive models [43]. The two conditions will also be compared on body weight and secondary outcomes at the 2-year follow-up relative to baseline to examine long-term maintenance. The analysis for this outcome will be similar to those conducted for body weight at 6 months and 1-year.

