### Research Goals

The present study aims to compare the efficacy of a sequential two-part treatment, behavioral activation for depression followed by standard weight loss treatment (BA), to standard weight loss treatment that is not accompanied by depression counseling (ST) on weight change in depressed, obese women. The primary hypothesis is that participants in the BA condition will achieve greater weight loss than participants in the ST condition at 6-months and 1- and 2-year follow-up. Secondary research goals include comparing groups on change in depression, physical activity, daily caloric intake, psychosocial variables (emotional eating, quality of life), and cardiovascular risk factors (blood pressure, serum lipids, C-reactive protein and waist circumference) at 6-months and 1- and 2-year follow-up. Additionally, potential mediators (treatment adherence, depression, physical activity, caloric intake) of the intervention effect on weight change will be tested.

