### Intervention

Both ST and BA conditions will involve an Intensive Treatment and a Maintenance phase. The Intensive Treatment phase will last 6-months and involve 26 sessions. Ten sessions will be 1-hour individual visits, and 16 sessions will be 1.5-hour group behavioral weight loss visits conducted by a registered dietitian or exercise physiologist. The timing of the individual and group visits varies between the two conditions. In the BA condition, participants will begin with 10 weekly individual visits of behavior therapy for treatment of depression, with the initial group behavioral weight loss visits starting on week 9. Participants in the ST condition will begin both the group behavioral weight loss visits and individual health education visits on week 1 (see Tables 3 and 4 for the timing of individual and group sessions in each condition) for two reasons. First, paralleling the BA condition (i.e., first 8-weeks of individual visits of health education attention control only) could lead to differential attrition rates since ST participants may not stay engaged when active treatment is delayed for 8 weeks. Second, this approach is also more consistent with usual care, in which participants would be enrolled and begin treatment immediately.

**Table 3 T3:** Distribution of treatment sessions by condition during the first 12 weeks of the 6-month Intensive Treatment phase.

Week	**1**	**2**	**3**	**4**	**5**	**6**	**7**	**8**	**9**	**10**	**11**	**12**
**ST**	I/G	G	G	G	I/G	G	G	G	G	G	I	G
**BA**	I	I	I	I	I	I	I	I	I/G	I/G	G	G

Note. ST = Standard treatment; BA = Behavioral Activation; I = Individual visit; G = Group visit

**Table 4 T4:** Distribution of treatment sessions by condition during the second 12 weeks of the 6-month Intensive Treatment phase.

Week	**13**	**14**	**15**	**16**	**17**	**18**	**19**	**20**	**21**	**22**	**23**	**24**
**ST**	I	G	I	G	I	G	I	G	I	G	I	I
**BA**	G	G	G	G	G	G	G	G	G	G	G	G

Note. ST = Standard treatment; BA = Behavioral Activation; I = Individual visit; G = Group visit

The 18 month Maintenance phase will consist of 6 monthly 90-minute group sessions and 6 monthly 20-minute counseling phone calls by their therapist or health education counselor, depending on their condition assignment. Then, participants will receive 20-minute counseling phone calls once every 3 months for one year. All visits in both phases will be audiotaped for quality assurance.

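### The protocol gives the primary weight comparison different sets of time points, is powered at 1 year only, and names no deciding visit or contrast for its interaction test

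*Protocol article*

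**What the plan says.** All places are in the protocol article.

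- **Research Goals.** Superiority of BA is the main hypothesis for all three visits: "participants in the BA condition will achieve greater weight loss than participants in the ST condition at 6-months and 1- and 2-year follow-up". Outcomes and Study Measures gives the same three time points as the main focus of the weight analyses.
- **Primary and Secondary Hypotheses-Analysis Plan.** Here only two visits are named: "The primary outcome compares body weight between the two randomized groups at 6-months and 1-year follow-up using an intent-to-treat analysis". The 2-year weight comparison comes later in that section, as a separate look at long-term maintenance. The test is of time-by-group interactions in a linear mixed model, to see whether within-person weight change differs by condition. The section adds: "In addition, we will model percent change in body weight at 6-, and 12-months using a similar model".
- **Sample Size.** Power is put at roughly 90%, and the figure was reached by "assuming a weight change difference of 3.1 kg at 1-year (standard deviation = 5.5 kg) and a 25% loss-to-follow-up rate". The Abstract repeats this and also refers to 1 year alone.
- **Intervention.** BA begins with individual therapy, "with the initial group behavioral weight loss visits starting on week 9". ST begins its weight-loss groups in week 1.

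**The concern.** The hypothesis and outcomes sections include 2 years in the primary comparison and the analysis plan leaves it out. Neither ranks 6 months against 1 year, yet the sample size rests on 1 year alone. The planned test does not settle the matter, because an interaction across several visits can be read as a set of visit-specific contrasts or as one joint test.

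What is at stake is which result decides the trial. If the choice is left open until outcome data are seen, the visit or the form of the test can be chosen afterwards. The staggered start sharpens this. At 6 months the two arms are at different points in their weight-loss programme by design, so a 6-month difference may reflect timing and not a lasting effect of treating depression first.

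**Working it through.** **1. Time points side by side**

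| Section | Time points | Role given |
|---|---|---|
| Research Goals | 6 months, 1 year, 2 years | primary hypothesis |
| Outcomes and Study Measures | 6 months, 1 year, 2 years | main focus for weight |
| Analysis Plan | 6 months, 1 year | primary comparison |
| Analysis Plan | 2 years | separate maintenance comparison |
| Abstract, Sample Size | 1 year | basis of power |

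**2. The stated power**

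Inputs from Sample Size: 87 per arm, 25% loss, difference 3.1 kg, SD 5.5 kg. Alpha and sidedness are not stated; two-sided 5% is assumed.

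- n = 87 × 0.75 = 65.25, taken as 65 per arm.
- SE = 5.5 × √(2/65) = 0.965 kg.
- Power = Φ(3.1/0.965 − 1.96) = Φ(1.25) = 89.5% (t-test version 89.0%).

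The stated 90% reproduces for a single two-group comparison at 1 year.

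**3. Reading (a): each visit tested at 5%, any one counts**

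The protocol gives no correlation between change scores at different visits, so 0.5–0.8 is assumed. Simulated probability of at least one |z| > 1.96 under no effect at any visit:

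| Correlation | Two visits | Three visits |
|---|---|---|
| 0.5 | 9.1% | 12.6% |
| 0.65 | 8.6% | 11.4% |
| 0.8 | 7.8% | 9.9% |

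If instead 6 months and 1 year must both be significant, error is not inflated and power becomes the issue. It is 82–85% if the true difference is 3.1 kg at both visits, and about 35–36% if the 6-month difference is 1.55 kg (an assumed half of 3.1).

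**4. Reading (b): one omnibus interaction**

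With time categorical and visits at baseline, 6 and 12 months, this is a 2-df test. For a true gap d at 6 months and none at 1 year, the non-centrality is λ = (d/SE)² / (1 − ρ²). For d = 2 kg:

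- (2/0.965)² = 4.30
- ρ = 0.5: λ = 4.30/0.75 = 5.73, rejection 56%
- ρ = 0.8: λ = 4.30/0.36 = 11.9, rejection 88%

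| Assumed 6-month gap, none at 1 year | Rejection, ρ = 0.5 to 0.8 |
|---|---|
| 1 kg | 17–32% |
| 2 kg | 56–88% |
| 3.1 kg | 92% to above 99% |

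Because d enters squared, the result is the same whichever arm is ahead. Adding the 2-year visit (3 df) gives 55–92% for 2 kg.

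**5. Why a 6-month gap is plausible here**

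Cumulative group sessions counted from Tables 3 and 4:

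| Week | 8 | 12 | 16 | 20 | 24 |
|---|---|---|---|---|---|
| ST | 8 | 11 | 13 | 15 | 16 |
| BA | 0 | 4 | 8 | 12 | 16 |

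By week 24 the number of sessions is equal. Time since weight-loss treatment began is not: 24 weeks in ST, 16 in BA (weeks 9–24). The documents do not say how large a weight gap this leaves at 6 months.

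**6. A single 1-year contrast**

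Its rejection rate is 5% when the arms are equal at 1 year, whatever the 6-month gap, and its power at 3.1 kg is the 89–90% of step 2.

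**The case against.** The strongest reply has five parts.

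- **A sample-size statement does not define a primary comparison.** Powering on one visit does not contradict analysing others. This stands. The outright conflict is over 2 years; the power statement only shows which visit the design rests on.
- **The interaction may already contain the right contrast.** With baseline and categorical time in the model, the condition-by-1-year term is the difference in change at 1 year. An unseen analysis plan may name it. This also stands: the model is sound. But such a plan would not make the protocol's own sections agree.
- **The two harms exclude each other.** A reader might infer that the trial suffers both familywise inflation and the timing problem. The documents do not support that. One omnibus test has no inflation across visits, and separate tests leave no omnibus result for the 6-month gap to drive. Nor is the any-one-counts rule stated; the hypothesis joins its time points with a plain conjunction.
- **The 56–88% is not a false-positive rate.** If a 6-month gap is real, rejecting equal trajectories is correct. The hypothesis also favours BA, so a result with ST ahead would not by itself support success. The figure shows only that a significant omnibus test need not mean a 1-year difference. The staggered start is explained in the Intervention section and is part of the strategy under test, so the 6-month comparison from randomisation remains valid for that strategy.
- **The omnibus test need not cost much power.** With 3.1 kg at 1 year and 1.55–3.1 kg at 6 months, its power is 83–92% for correlations 0.5–0.8. This is correct.

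A reader might also infer that the percent-change model would miss a constant benefit. That holds only if it uses just the 6- and 12-month values and tests the interaction alone. The protocol calls it a similar model and says neither.

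**Conclusion.** The point holds as an inconsistency that should be fixed. The protocol's sections disagree on whether 2 years is primary, none ranks 6 months against 1 year, and the interaction test has no named deciding visit or contrast, although only 1 year is powered. The sample-size arithmetic is sound.

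The consequence depends on the reading. It is either a familywise error of about 8–9% (two visits) or 10–13% (three visits), or an omnibus test that a 6-month difference alone can make significant; it is not both. The sizes rest on two-sided 5%, 65 per arm, SD 5.5 kg at every visit, and correlations of 0.5–0.8. The omnibus illustration further assumes categorical time and a 2 kg gap at 6 months. The true gap is unknown, and the equal session counts by week 24 mean that it could be small. The documents do not support the claim that the delayed start will produce a false-positive trial.

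**What to change.** Name one primary test: the between-condition difference in weight change from baseline to 1 year, estimated as a single contrast from the planned mixed model with time as a categorical factor, at two-sided 5%. Make 6 months and 2 years secondary, and align Research Goals, Outcomes and Study Measures, and the analysis plan with this. Report percent change by the same 12-month contrast. When presenting the 6-month result, note that BA is then 16 weeks and ST 24 weeks from the start of weight-loss treatment.

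The change is to wording only. It needs no more participants and keeps the stated power, but should be settled before outcome data are seen. The cost is that success can no longer be claimed on 6 months or 2 years alone.

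### The 90% power holds only if women are independent, and the primary model as written names no treatment-group term, although weight-loss treatment is delivered in groups that in effect sit within one condition

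*Protocol article*

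**What the plan says.** **Delivery.** Under Intervention, the Protocol article has 26 intensive sessions, of which "16 sessions will be 1.5-hour group behavioral weight loss visits conducted by a registered dietitian or exercise physiologist". Six monthly group sessions follow in the maintenance phase. In the behavioral activation (BA) condition individual therapy comes first, "with the initial group behavioral weight loss visits starting on week 9". By contrast, "Participants in the ST condition will begin both the group behavioral weight loss visits and individual health education visits on week 1" (ST being standard treatment). The ST Condition section confirms the difference in timing ("Although the timing of the group visits will differ between conditions") and says that the content is the same. The Treatment Fidelity section refers to treatment waves, so there is more than one cohort.

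**Power.** Under Sample Size: "This study will randomize 174 participants into two conditions (87 per condition) who will be followed for 2 years". The claim is "We expect approximately 90% power for detecting differences in weight between the conditions". It rests on three inputs: 3.1 kg between conditions after one year, an SD of 5.5 kg, and a quarter of the women lost. No group size, ICC or design effect is mentioned.

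**Model.** Under Primary and Secondary Hypotheses-Analysis Plan: "Linear mixed modeling, using SAS PROC MIXED [41] will test time and group interactions", with the aim of judging whether within-subject change differs by condition. No term for treatment group, wave or counselor is named.

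**The concern.** Women who share leaders, discussion and group exercise over 16 or more sessions can be expected to end up somewhat alike in weight change. Randomizing individuals does not remove a correlation that arises after randomization. When whole treatment groups belong to one condition, a positive correlation adds between-group variance directly to the treatment contrast. An analysis that allows only for repeated measures on the same woman then understates the standard error, and a sample size worked out for independent women overstates the power. At stake are the error rate of the primary test and the credibility of the only power figure in the article.

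**Working it through.** **Step 1. Are treatment groups nested within condition?** From Tables 3 and 4:
- ST group visits fall in weeks 1-10, then in weeks 12, 14, 16, 18, 20 and 22: 10 + 6 = 16.
- BA group visits fall in every week from 9 to 24: 16.

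Starting an ST wave eight weeks after a BA wave would align the first ten sessions. After session 10, ST meets every second week and BA every week, so no shared group could follow the ordered 16-session curriculum of Table 5. No sentence says that groups are condition-specific, but the intensive-phase calendars leave little else. The article does not give maintenance groups by condition.

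**Step 2. Reproduce the stated power.** Inputs from Sample Size: difference 3.1 kg, SD 5.5 kg, 87 per condition, 25% loss. Two-sided 5% is assumed, as alpha is not stated there.
- Completers per condition: 87 × 0.75 = 65.25.
- SE = 5.5 × √(2/65.25) = 0.963 kg.
- Power = Φ(3.1/0.963 − 1.96) = Φ(1.26) = 89.6%. The noncentral t with 65 or 66 per condition gives 89.0% or 89.5%.

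This matches the stated figure with a design effect of 1. There is no slack: a full 90% needs 67 completers, and 67/0.75 rounds up to 90 randomized per condition, against 87.

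**Step 3. Allow for treatment groups.** Group size m and ICC are assumptions. Dropout is applied to the group as well as to the total.
- Design effect: DE = 1 + (0.75m − 1) × ICC.
- Power = Φ(3.1/(0.963 × √DE) − 1.96).
- Type I error if grouping is ignored = 2 × (1 − Φ(1.96/√DE)).
- The last column uses a t reference on 2(k − 1) degrees of freedom, with k = 87/m groups per condition.

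| m | ICC | DE | Power (normal) | Type I error if ignored | Power (group-level df) |
|---|---|---|---|---|---|
| 8 | 0.01 | 1.05 | 88.1% | 5.6% | 84.8% |
| 8 | 0.02 | 1.10 | 86.6% | 6.2% | 83.1% |
| 8 | 0.05 | 1.25 | 82.1% | 8.0% | 78.1% |
| 10 | 0.01 | 1.065 | 87.7% | 5.8% | 83.2% |
| 10 | 0.02 | 1.13 | 85.7% | 6.5% | 80.9% |
| 10 | 0.05 | 1.325 | 79.9% | 8.9% | 74.5% |
| 12 | 0.01 | 1.08 | 87.2% | 5.9% | 81.4% |
| 12 | 0.02 | 1.16 | 84.8% | 6.9% | 78.6% |
| 12 | 0.05 | 1.40 | 77.7% | 9.8% | 70.8% |

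Example, m = 12 and ICC 0.05: DE = 1 + (9 − 1) × 0.05 = 1.40, √DE = 1.183, and power = Φ(3.1/(0.963 × 1.183) − 1.96) = Φ(0.76) = 77.7%.

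A design effect of about 1.05 takes power to 88%, and about 1.32 takes it to 80%.

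**The case against.** **The article is not the full plan.** One sentence describes the model, and the reference to within-subject change says what is compared, not which random effects are fitted. A full protocol or analysis plan may well contain a treatment-group term. This stands. It follows that the article does not show the standard errors to be wrong; they are wrong only if the model is run as written and the ICC is above zero. The power figure is different: the article prints it together with its inputs, and a group term added elsewhere would not restore it.

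**The ICC may be very small.** It may. With groups of 8 and ICC 0.01, power is 88.1% by the normal approximation, less than 2 points below a figure that is itself only approximate.

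**The SD is described as conservative.** If the true SD were 5.0 kg (an illustration, not a figure from the article), power would be about 92% at a design effect of 1.10 and 87% at 1.325. The article does not say how much margin the 5.5 kg holds, so this may offset the loss but cannot be counted on to do so.

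**A stronger reading.** A reader might infer that the intervals are certainly too narrow, or might reach power as low as 72-73% and type I error near 12% by using a design effect of 1.55 (full groups of 12, ICC 0.05: 1 + 11 × 0.05). The documents do not support either. The first needs a positive ICC and the absence of a group term in the full plan. The second takes dropout off the sample but not off the group size.

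**Conclusion.** The point holds in conditional form. The intensive-phase calendars in effect nest treatment groups within condition, and the stated power contains no allowance for this. Any positive within-group correlation therefore puts power, on the plan's own inputs, below the stated figure, and the primary model run as written would be anti-conservative.

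The loss is small at ICC 0.01 and material towards ICC 0.05, where the normal approximation reaches 78% in groups of 12. Power is lower again once the test has group-level degrees of freedom. These sizes rest on assumed ICCs of 0.01-0.05, assumed groups of 8-12, a two-sided 5% test, and groups that stay within one condition.

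**What to change.** 1. In the primary PROC MIXED model, specify a random effect for treatment group (wave within condition) with small-sample degrees of freedom such as Kenward-Roger, unless the full plan already does so. The effect has to act on change: if baseline weight is one of the repeated outcomes, a group intercept constant over time cancels from the change contrast, so a treatment-group-by-visit term is needed.
2. Make sure that each woman's assigned treatment group is in the analysis data set. The tracking system already holds intervention data, so this should be a matter of confirming a field.
3. Restate power with an explicit ICC and group size, preferably as a short range.

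**Cost.** A small change to the model code and a less favourable stated power. Over the range above, the standard error is 1.02 to 1.18 times the one that ignores grouping, and the critical value is somewhat larger, so intervals widen slightly if the ICC is small and more if it is not. No extra participants are needed for this fix, but it restates the power and does not restore it. Holding 90% would take about 94 to 126 per condition over the same range (67 × DE/0.75, normal approximation) instead of 87.
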